#### Sample processing, storage and transport of samples

Blood samples for glucose measurement will be collected in vacutainers with sodium
fluoride, centrifuged and separated into two cryovials (aliquots) immediately and
transported in an icebox maintained at 4­8°C to the central laboratory for
immediate testing (within 8 hours of collection). Whole blood samples for full
blood count and HbA1c will be collected in vacutainers containing EDTA. Plasma glucose,
full blood count and HbA1c measurements will be performed at the central biochemistry
and clinical diagnostic laboratory services laboratory at the Medical Research
Council/Uganda Virus Research Institute (MRC/UVRI) and London School of Hygiene and
Tropical Medicine (LSHTM) Uganda Research Unit Entebbe, Uganda. Laboratory analyses will
be performed on the Roche Cobas 6000 analyser (Hitachi high technologies corporation,
Tokyo, Japan). Plasma glucose will be measured by the glucokinase method. HbA1c will be
measured on Cobas 6000 by the immunoassay technique, calibrated to the International
Federation of Clinical Chemistry. Serum and plasma samples will be centrifuged
immediately and divided into cryovials for long-term storage at −80°C (see
table 3 for further details).

**Table 3 T3:** Sample processing and storage

Sample	Processing
5 mL serum separating tube	The tube will be immediately spun, and the serum will be aliquoted into five 2 mL microvials (cryovials). The cryovials will then be placed in a cool box at 4–8°C until shipment to the central laboratory, where they will be stored in a −80°C freezer.
2 mL NaF blood tube (all)	Blood tubes will gently be inverted to mix and then spun within 15 min of blood draw, aliquoted into 2 mL cryovials and then placed in a cool box at 4–8°C until shipment to the central biorepository for measurement of plasma glucose.
2 mL EDTA	The tube will be inverted gently to mix. This tube will be transported to the central laboratory for HbA1c and CBC testing uncentrifuged.
4 mL EDTA whole blood tube	The tube will be gently inverted to mix. It is not centrifuged. Blood is aliquoted into 5 mL cryovials and transported to the central laboratory for immediate storage at −80°C for future genetic testing.

CBC, complete blood count; HbA1c, glycated haemoglobin; NaF, sodium fluoride.

### Definitions

Diabetes will be defined according to WHO guidelines as a fasting venous capillary plasma
glucose ≥7.0 mmol/L, a 2-hour post-load venous plasma glucose
≥11.1 mmol/L, HbA1c ≥48 mmol/mol (6.5%) or on oral or
insulin treatment for diabetes. Pre-diabetes will be defined as a fasting venous or
capillary plasma glucose between 5.6 and 6.9 mmol/L, a 2-hour post-load venous
plasma glucose between 7.8 and 11.0 mmol/L or HbA1c between 42 and
47 mmol/mol (6.0–6.4%).^13–15^

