## Abstract

**Introduction:**

Sub-Saharan Africa is experiencing an increasing burden of diabetes, but there are
little reliable data, particularly at the community level, on the true prevalence or why
this condition affects young and relatively lean individuals. Moreover, the detection of
diabetes in Africa remains poor, not only due to a lack of resources but because the
performance of available diagnostic tests is unclear.

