**Design:**

This is a population-based study nested within the longstanding general population
cohort in southwestern Uganda. We will undertake a population survey to identify
individuals with diabetes based on fasting glucose, HbA1c, OGTT results or history of
pre-existing diabetes.

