**Participants:**

The study intends to enrol up to 11 700 individuals aged 18 years and above,
residing within the study area and not pregnant or within 6 months post-delivery
date. All participants will have detailed biophysical and biochemical/metabolic
measurements. Individuals identified to have diabetes and a random selection of controls
will have repeat tests to test reproducibility before referral and enrolment into a
diabetic clinic. Participants will then be followed up for 1 year to assess the
course of the disease, including response to therapy and diabetes-related
complications.

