## Introduction

Diabetes is a global problem disproportionately affecting low-income and middle-income
countries (LMICs). According to the 2021 International Diabetes Federation estimates,
80% of the approximately 537 million adults (20–79 years) living with
diabetes reside in LMICs.^1^ In sub-Saharan Africa
(SSA), an estimated 24 million people are living with diabetes, which is projected to
reach 55 million within 20 years.^1^ Moreover,
the region is said to harbour the highest proportion of undiagnosed patients with
diabetes.^1^ This poses a major threat to sustained
development in the region if resources have to be found to treat the complications of this
condition.

An effective response will require a clear understanding of the burden, important local
determinants of risk, and pathophysiological and clinical manifestations of diabetes.
However, there are limited Africa data, with most coming from relatively small studies using
unstandardised methodologies. This may explain the significant variation in diabetes
prevalence observed between countries.^2^ Moreover,
there are concerns that some of the widely used tests to diagnose and monitor diabetes may
be unreliable in Africa. Although still a relatively unexplored area, the clinical utility
of glycated haemoglobin (HbA1c) in SSA has been questioned due to the high prevalence of
haemoglobinopathies such as sickle cell trait and other medical conditions that might affect
test reliability, including anaemia, malaria and HIV infections.^3–6^ Similarly, there are concerns about the utility of
oral glucose tolerance test (OGTT), the current gold-standard test for diagnosing
diabetes.^7^ It is not only complex and expensive but
may have other important limitations, such as the need to have adequate caloric intake in
the days preceding the test. Our preliminary study showed that a missed or small meal the
night before a test could lead to falsely elevated glucose.^8^ This might explain why some Africa studies have found a high prevalence of
diabetes or glucose intolerance where OGTT has been used. Therefore, OGTTs cannot be fully
relied on to screen for diabetes in settings where food insecurity or missed evening meals
are common.

There is also increasing evidence that diabetes may manifest differently in Africa compared
with its presentation in high-income countries. For example, while traditionally, type 2
diabetes is considered a disease of old age associated with obesity and insulin resistance,

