Phase IV	In this phase, we aim to establish well-characterised people with and without diabetes. The newly diagnosed participants with diabetes will be referred to the local diabetes clinics, where they will be managed according to the Uganda Ministry of Health guidelines. The newly diagnosed patients with diabetes and those with known diabetes will be followed up in clinics (supported by the research team) to study the *course of the condition*, including; (1) response to treatment: participants will be followed up at the clinic to assess glycaemic control (HbA1c) every 3 months, determine the time to treatment intensification (need for dosage increment, the addition of another drug or switching from oral hypoglycaemic agents to insulin), and (2) assess disease progression *through* (a) measuring of endogenous insulin secretion (using mixed meal tolerance tests), (b) assessment of insulin resistance and repeat vascular complications reassessment (including retinopathy, nephropathy). Concurrently, participants with pre-diabetes and those with normal glucose levels will be followed in a longitudinal study nested in the GPC to determine the incidence of diabetes.

GPC, general population cohort; HbA1c, glycated haemoglobin; OGTT, oral glucose
tolerance test.

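### A single raised value on any of three doubted tests counts as diabetes in the primary prevalence, so false positives may add as much as or more than the planned ±0.5 points, and the role of the repeat test is not fixed

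*Protocol article*

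**What the plan says.** **Case rule.** In Definitions, "Diabetes will be defined according to WHO guidelines as a fasting venous capillary plasma" glucose at or above 7.0 mmol/L is one of four alternatives joined by 'or'. The others are a 2-hour glucose of at least 11.1 mmol/L, an HbA1c of at least 48 mmol/mol, and treatment for diabetes. The Abstract (Design) has the same structure: the survey identifies "individuals with diabetes based on fasting glucose, HbA1c, OGTT results or history of" known disease. Neither asks for a second abnormal value.

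**Estimator.** Statistical considerations computes diabetes prevalence as cases divided by participants enrolled. It states no adjustment for misclassification.

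**Doubts about the tests.** The Abstract gives as one reason for poor detection that the "performance of available diagnostic tests is unclear". The Introduction says "there are concerns that some of the widely used tests to diagnose and monitor diabetes may" be unreliable in Africa. It says the clinical utility "of glycated haemoglobin (HbA1c) in SSA has been questioned due to the high prevalence of" haemoglobinopathies and other conditions. It also reports that a missed or small meal the "night before a test could lead to falsely elevated glucose", and concludes that the OGTT cannot be fully relied on for screening where this is common. The OGTT section states a check of the 8-hour fast and none of the evening meal.

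**Repeat tests.** The Abstract (Participants) says people identified with diabetes and randomly chosen controls "will have repeat tests to test reproducibility before referral and enrolment into a" diabetic clinic. Table 2, Phase II, describes repeat testing in a randomly selected set of participants. Table 2, Phase IV, refers newly diagnosed participants to clinics without a confirmation criterion. To assess response to treatment, "participants will be followed up at the clinic to assess glycaemic control (HbA1c) every 3 months".

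**The concern.** The false-positive rates of several tests accumulate under an 'or' rule. When about 95 in 100 people do not have the disease, a small loss of specificity adds cases that are many relative to the true ones. The protocol itself names a mechanism that pushes glucose upward, then counts the resulting values in its primary outcome. The ±0.5-point precision covers sampling error only, so enrolling more people does not reduce this error.

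A second issue follows. Someone labelled on glucose alone may already have an HbA1c below 48 mmol/mol, and a one-off high value tends to fall on re-measurement without treatment. If such people enter Phase IV, their HbA1c course says little about treatment. Whether they enter depends on what a normal repeat test does, and the protocol does not settle that.

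**Working it through.** **1. The plan's own figure.** Sample size determination uses prevalence p = 5%, margin d = 0.5 points and z = 1.96.

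n = z² p(1−p)/d² = 1.96² × 0.05 × 0.95 / 0.005² ≈ 7,299, stated as 7300. Then 7300/0.8 × 1.2 = 10 950. Both reproduce.

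**2. Formula for misclassification.** With true prevalence π, and sensitivity Se and specificity Sp of the whole rule:

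- observed prevalence = π·Se + (1−π)(1−Sp)
- bias = (1−π)(1−Sp) − π(1−Se)

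Let s be the specificity of each test. If the three tests err independently, Sp = s³. If their errors overlap completely, Sp = s. The protocol gives no value for s or Se, so both are assumptions.

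**3. Bias at π = 5% and Se = 1.** The share of labelled cases that are false is in brackets.

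| s per test | Full overlap: 95 × (1−s) points | Independent: 95 × (1−s³) points |
|---|---|---|
| 99.9% | 0.095 (2%) | 0.28 (5%) |
| 99.5% | 0.48 (9%) | 1.42 (22%) |
| 99% | 0.95 (16%) | 2.82 (36%) |
| 98% | 1.90 (28%) | 5.59 (53%) |

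Worked entry: at s = 99.5% with independence, 1 − 0.995³ = 0.01493, and 95 × 0.01493 = 1.42 points. The false share is 1.42/6.42 = 22%.

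**4. Where the bias reaches the stated precision.** Setting 0.95 × (1−Sp) = 0.005 gives a combined specificity of 99.47%. Under independence that is 99.82% per test.

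**5. Imperfect sensitivity.** If the whole rule has 80% sensitivity, missed cases remove 5 × 0.2 = 1.00 point.

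- s = 99%: 0.95 − 1.00 = −0.05 to 2.82 − 1.00 = +1.82 points.
- s = 99.5%: 0.475 − 1.00 = −0.525 to 1.42 − 1.00 = +0.42 points.

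An 'or' rule tends to raise combined sensitivity, which limits this offset but does not remove it.

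**6. Lower true prevalence.** The 5% is explained as a doubling, but twice the cited survey figure of 1.4% is 2.8%. At π = 2.8%, s = 99% and Se = 1, observed prevalence is 2.8 + 0.97 = 3.77% (overlap) to 2.8 + 2.89 = 5.69% (independent). False shares are 26% and 51%.

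**7. What a confirmed count could show.** Take π = 5%, s = 99%, independent errors, and assume that all true cases confirm. If a false positive recurs with probability 0.1, 0.3 or 0.5, the headline of 7.82% compares with a confirmed prevalence of 5.28%, 5.85% or 6.41%.

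**8. Repeat-test passages side by side.** The Abstract repeats those identified with diabetes plus random controls, whereas Table 2 (Phase II) repeats a random set. The purpose in both is reproducibility. Definitions and Table 2 (Phase IV) do not mention a repeat result. No section says how a case with a normal repeat is classified.

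**The case against.** **The rule is a recognised one, and breakdowns belong in an analysis plan.** The definition follows the WHO guidance that the study adopts, and an article may leave tables by test or by concordance to documents not shown. This stands as far as it goes: their absence alone would be no finding. But the case rule and the estimator of the primary outcome are fixed here, the doubts about the tests are stated here, and the conflict over repeat testing lies within this document.

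**Agreement between tests is already planned.** The Introduction plans to compare fasting glucose and HbA1c with the OGTT, and Statistical considerations plans agreement and reproducibility statistics. That is correct, but nothing links those results to the case count.

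**The size is assumed.** This stands. The independent-error figures are an upper end, because fasting and 2-hour glucose come from one session. With overlap, 99.5% gives 0.48 points and not 1.42. Imperfect sensitivity could cancel the bias. Only the glucose error has a stated upward direction: the HbA1c error has none, and fasting glucose is not singled out. A false positive also presupposes a reference standard. The Introduction calls the OGTT the gold standard while doubting it, so the figures refer to an unobserved true state.

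**A stronger reading is not supported.** A reader might infer that false positives pass unfiltered into Phase IV and appear there as good treatment responders. The documents do not establish this. The Abstract places repeat tests before referral, the participant-flow figure is not shown, no responder definition is given, and Phase IV also measures time to treatment intensification, insulin secretion, insulin resistance and complications. Unfiltered entry is neither stated nor excluded.

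**Conclusion.** The concern holds in a limited form. One raised value on any of three tests makes a case, and the primary prevalence counts such cases without stated confirmation or correction, although the protocol describes a way in which glucose can be falsely raised. At 5% prevalence with perfect sensitivity, the added amount is 0.48 to 1.42 points at 99.5% specificity per test and 0.95 to 2.82 points at 99%, against a planned precision of ±0.5. These are ranges under assumed specificities, running from fully overlapping to independent errors, and are not estimates for this population. Net upward bias is likely but not certain.

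Separately, and without any assumption, the Abstract and Table 2 disagree on who is repeat-tested, and no section says whether a normal repeat changes case status or Phase IV entry. An effect on the Phase IV treatment-response results is a reasonable inference whose size cannot be derived.

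**What to change.** 1. Keep the WHO-based 'or' definition as the headline prevalence.
2. Beside it, report the prevalence of untreated cases by which test or tests were positive, and by concordance. Count a case as concordant if HbA1c and a glucose criterion are both met, or if it is positive again on repeat where a repeat was done. Show fasting plus 2-hour glucose from the same session separately, because both may carry the missed-meal error.
3. Report HbA1c-only cases by anaemia status from the blood count already taken.
4. Reconcile the Abstract (Participants), Definitions, and Table 2 Phases II and IV on who is repeat-tested and what the result does to case status and Phase IV entry.
5. In Phase IV, present HbA1c response among newly diagnosed participants by baseline concordance and baseline HbA1c as a sensitivity analysis. It should not become the main set: restricting to a baseline HbA1c of at least 48 mmol/mol would select on a test that the protocol doubts and would itself induce regression to the mean.

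Items 1 to 3 and 5 are analysis classifications that use data already planned and leave referral and care as they are. The cost is wording, a concordant prevalence below the headline that will need explaining, and smaller subgroups. If only a random set is repeated, confirmation by repeat will be known for some cases only, and the report should say so.

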### Sample size determination

This study is powered to estimate the prevalence of diabetes and pre-diabetes with a high
degree of precision. We base our assumptions on results from the 2014 Ugandan nationwide
cross-sectional survey suggesting that the prevalence of impaired fasting glucose and
diabetes in Uganda is 2% (95% CI: 1.5% to 2.5%) and
1.4% (95% CI: 0.9% to 1.9%), respectively.^16^

Applying a rule of thumb that the margin of error should not exceed 0.25 of the
prevalence, and based on the following assumptions: (1) a margin of error of 0.5%
(a margin of error of 0.5–1% would be acceptable for low prevalence
conditions), (2) diabetes prevalence of 5% (assuming OGTT would detect twice more
cases of diabetes thus doubling the prevalence) and an estimated 5% level of
significance (z-value=1.96).

The minimum sample size is 7300 for a precision of ±0.5% and a
significance level of 5%. Assuming a response rate of 80% and further
adjusting for a design effect at 1.2, the required sample size of
(7300/0.8)×1.2=10 950. Therefore, we will aim to randomly screen a minimum
of 10 950 adults across all study sites.

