### Sample population

The GPC is a rural population-based open cohort study of people living within the 25
villages of the Kyamulibwa subcounty. The population in Kyamulibwa is assessed routinely
during annual surveys as part of the census and 2-year medical surveys. The entire adult
population of the GPC will be invited to participate in this study. Data from the most
recent census in the GPC study villages show that there are 8864 adults out of the total
population of 20 751. A recent enumeration for a COVID-19 survey conducted in
Lukaya established that there are approximately 10 000 adults in all the five
villages. All these will be invited to take part in our study. The combined adult
population within the GPC and Lukaya will give us enough power to rigorously examine our
primary objectives, allow explorations of the outcomes and key risk factors, and establish
long-term cohorts.

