### Sampling strategies

Recruitment will be restricted to individuals who reside within defined study areas.
Research team members (mobilisers) will visit each household in the study areas. All
adults aged 18 years and above will be invited to take part in the study (table 1). We will recruit every adult who is able and
willing to consent and is a resident at a household (ie, not a temporary member with
intent to leave) in the study areas. The participant’s flow in the study is shown
in figure 1.

**Table 1 T1:** Eligibility criteria for the participants enrolled into the DOP Study

Inclusion criteria	Individuals aged 18 years and above
	Individuals residing within the study area for the past 6 months
	Individuals willing to provide informed consent
Exclusion criteria	Pregnant women and women within 6 months post-delivery
	Participants unwilling to give informed consent
	Living outside the geographical sampling frame for the relevant site

DOP, Diabetes in low-resource Populations.

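### The survey is described as a census of about 18 864 adults, but also as random screening and as enrolling up to 11 700; at the plan's own 80% response these do not fit together

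*Protocol article*

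**What the plan says.** Four places in the protocol article bear on who enters the survey.

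- **Sample population.** The whole adult population of the rural general population cohort (GPC) is to be invited; the "recent census in the GPC study villages show that there are 8864 adults out of the total" population. For the periurban site, an enumeration in "Lukaya established that there are approximately 10 000 adults in all the five" villages. The section then adds: "All these will be invited to take part in our study".
- **Sampling strategies.** "Research team members (mobilisers) will visit each household in the study areas". "We will recruit every adult who is able and" willing to consent, provided that the adult is a resident. Table 1 excludes pregnant women, women within 6 months of delivery and people with less than 6 months' residence.
- **Sample size determination.** A minimum of 7300 is divided by an 80% response rate and multiplied by a design effect of 1.2, giving 10 950. The section ends: "Therefore, we will aim to randomly screen a minimum" of that many adults.
- **Abstract, Participants.** "The study intends to enrol up to 11 700 individuals aged 18 years and above".

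Statistical considerations then defines prevalence as cases divided by all participants enrolled, which is a crude proportion.

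**The concern.** Inviting everyone and recruiting everyone who agrees is a census. Random screening is a different design, with a draw and a known selection probability. The article describes no draw for the survey: it mentions random selection only for the controls and the reproducibility set.

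The 11 700 in the abstract adds a second difficulty. A census at 80% response would produce clearly more people than that, and the article does not say whether 11 700 is a limit or a forecast.

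The primary outcome is a prevalence estimated as a crude proportion of those enrolled. That proportion describes the population only if inclusion is complete, random or corrected for. A reader who takes the word *randomly* at face value would credit the confidence interval with a coverage that the described recruitment does not supply. The two sites are also included to explore differences between them (Study setting), so the mix of sites among those enrolled can matter for the pooled figure.

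**Working it through.** **Inputs from the article.** GPC adults 8864; Lukaya adults about 10 000; response 80%; design effect 1.2; prevalence 5%; margin 0.5%; z = 1.96; enrolment up to 11 700.

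**1. The plan's own figures reproduce.**
- n = z²p(1−p)/d² = 1.96² × 0.05 × 0.95 / 0.005² = 7299, stated as 7300.
- (7300 / 0.8) × 1.2 = 10 950, as stated.

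**2. What 10 950 counts.**
- The division by 0.8 is the non-response allowance, so 10 950 is a number to approach.
- The number to test is 7300 × 1.2 = 8760, and 10 950 × 0.8 = 8760 confirms it.

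**3. Precision under either reading.** Half-width = 1.96 × √(1.2 × 0.05 × 0.95 / n).

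| n tested | Half-width |
|---|---|
| 8760 | ±0.50% |
| 10 950 | ±0.45% |
| 11 700 | ±0.43% |

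**4. What a census would yield.**
- Invited: 8864 + 10 000 = 18 864.
- Accepting at 80%: 18 864 × 0.8 = 15 091.
- Excess over 11 700: 15 091 − 11 700 = 3391, or 3391 / 15 091 = 22.5% of willing adults.
- Uptake at which 11 700 is just reached: 11 700 / 18 864 = 62.0% of all adults.
- Uptake needed to enrol 10 950: 10 950 / 18 864 = 58.0%.

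**5. Allowing for ineligibility.** The article gives no share of adults who fail Table 1, so 5–15% is an assumption.

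| Ineligible (assumed) | Accepting at 80% | Response among eligible adults that gives 11 700 |
|---|---|---|
| 0% | 15 091 | 62.0% |
| 5% | 14 337 | 65.3% |
| 10% | 13 582 | 68.9% |
| 15% | 12 828 | 73.0% |

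For 11 700 to agree with 80% response, 11 700 / 0.8 = 14 625 adults must be eligible. That makes 1 − 14 625 / 18 864 = 22.5% ineligible.

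**6. Illustration only.** Suppose that the 22.5% of willing adults were left out and that their prevalence differed from that of enrolled adults by 1 or 2 percentage points (assumed, in either direction). The enrolled proportion would then miss the prevalence among all willing adults by 0.225 × 1 = 0.22 or 0.225 × 2 = 0.45 points. The planned margin is 0.5 points.

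**The case against.** Much can be said for the plan.

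- **A reader might infer that the three figures are mutually impossible.** They are not. 10 950 is a minimum and 11 700 an upper figure, so those two agree, and inviting 18 864 adults fits both if uptake lies between 58% and 62%. What does not fit is the stated 80% response, unless about 22.5% of adults are ineligible.
- **A reader might infer a hard cap that admits people by order of visit or availability.** The article gives no stopping rule, and Sampling strategies says that every willing resident is recruited. The figure stands only in the abstract and may be an expected yield. Selection by visiting order would follow only if the figure were enforced, because no other rule is given.
- **Applying 80% to every enumerated adult ignores Table 1**, and participants who have not fasted must come back another day, a further source of loss. This is right. It narrows the gap but does not close it at 5–15% ineligible.
- **The origin of 11 700 may be in the full protocol.** A condensed article need not derive it, so the missing derivation is not counted here.
- **Confusing approached with tested does no harm to precision.** This stands in full.
- **Bias is not demonstrated.** This stands too. Any figure rests on an assumed prevalence in people not seen, and part of it would be the ordinary non-response bias of any survey.

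What remains is that the article contradicts itself on the sampling design, and that its response assumption and its enrolment figure disagree.

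**Conclusion.** The point holds as a contradiction about who enters the primary denominator. The recruitment described is a census, and the word *randomly* has no procedure behind it.

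At 80% response, the census gives about 15 091 participants before ineligibility, or about 12 800 to 14 300 if 5–15% are ineligible. There are two readings of 11 700. It may be a ceiling, which would leave out willing adults with no stated rule. Or it may be an expected yield, which implies uptake of about 62% of all adults (about 65–73% of eligible adults on the same assumption). The article does not say which.

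The sample size arithmetic is sound and the ±0.5% margin is met whether 10 950 is read as approached or tested. The issue is representativeness, and the documents do not allow its size to be estimated; the 0.22 to 0.45 points above are illustrative. The totals rest on an approximate count for Lukaya and on an ineligible share that the article does not report.

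**What to change.** 1. Describe the survey as a census of resident eligible adults and delete the word *randomly*.
2. Remove 11 700 as a ceiling, or state that it is an expected yield and bring the response assumption into line with it.
3. Label 8760 as the minimum tested and 10 950 as the minimum approached.
4. Report response by site, over the enumerated eligible adults.
5. In place of only the crude proportion of those enrolled, report prevalence weighted to the enumerated adult population. By site this is the sum of (site adults / all adults) × site prevalence, with weights 8864 / 18 864 = 47.0% for the GPC and about 53.0% for Lukaya. Add sex and age group where those margins are available; for Lukaya the article gives only an approximate total.

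A random draw of households is not a workable alternative, because Study status says that enrolment began in January 2022.

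The cost is wording, a modest amount of analysis and a slightly wider confidence interval. Weighting corrects only for the margins used: it does not remove differences between enrolled and missing adults within the same site, sex and age group.
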